### Trial Management

The myAID study group, consisting of 2 gastroenterologists, 1 IBD clinical nurse consultant, 1 psychologist, and 1 research assistant, provides day-to-day oversight of the trial and meets at 1 to 2 weekly intervals to address any queries regarding the patient’s eligibility at the time of referral or logistical issues raised by participating sites. Each study site will have 1 lead clinician to oversee local patient referral activity and act as the liaison for the myAID study group, but sites will not be directly involved in any patient consent, data collection, or follow-up procedures, which will be entirely managed by the myAID study group. The myAID study group will not be involved in any test result interpretation, for example, colonoscopy or FC, treatment decisions, or advice about management, and any such queries from participants will be forwarded directly to the treating team.

### Safety Monitoring and Reporting

As the intervention in this trial does not include drug treatment or procedures, we do not anticipate any safety issues, although we will keep track of the treatment options being selected based on study participants’ reports.

### Withdrawal

Study participants will be able to withdraw from the study whenever they wish without giving a reason and without affecting their care. We will document their reasons for withdrawal if provided as well as any feedback regarding myAID. If a participant misses 1 assessment, we will encourage them to continue the study and complete the subsequent questionnaires and FC testing at the designated time points. Patients who undergo colectomy during the study period will remain in the study unless they specifically choose to withdraw. Data collection from these patients will be altered as previously described.

### Data Management and Record Keeping

The data acquired during the study will be coded and stored as deidentified data on a secure, password-protected computer located at the Ingham Institute for Applied Medical Research and accessed over a secure, virtual private network. Only the members of the myAID study group not directly involved in the participant’s care will have access to identifiable data except for the results of the FC, which will be forwarded directly to the referring clinicians.

### Sample Size and Power

The myAID study design is based on an assumption of 0.5 SD difference between the intervention and control groups for the primary outcome of QoL using the AQoL-8D utility score at 6 months. This estimate fares well with the published study by Gibson et al using AQoL-8D, which identified the scores between those in clinical remission and those with active UC [19]. The sample size has been adjusted for the design effect due to the cluster randomization assuming unequal cluster sizes and can accommodate an intraclass correlation coefficient (ICC) as high as 0.05 to achieve 80% power. Adjusting for this ICC, the estimated required sample size for the full study is 238 patients (119 per group), which will require a minimum of 14 clusters for sufficient recruitment. Assuming 70% of eligible patients consent to study participation and a loss to follow-up rate of 20% at the 6-month end point, we then aim to approach a minimum of 426 patients (213 per group) and recruit 298 patients at baseline.

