### Setting

This study will be undertaken at 22 sites in 5 of the 6 states in Australia, including large public IBD clinics and community-based private practices in urban and regional areas. Patient enrollment commenced in October 2016, with 21 of the 22 sites currently enrolling participants. All data collection (all participants) and viewing of myAID (intervention participants) will be undertaken off-site.

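### The stated 80% power does not hold for 238 patients in 14 clusters once the arm effect is tested on between-site degrees of freedom (about 75% at best), and the figure was not restated for the 22 sites now in the trial

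*Protocol article*

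**What the plan says.** The section Sample Size and Power in the protocol article is "based on an assumption of 0.5 SD difference between the intervention and control groups" in the AQoL-8D utility score at 6 months. It continues: "The sample size has been adjusted for the design effect due to the cluster randomization assuming unequal cluster sizes", and adds that the design "can accommodate an intraclass correlation coefficient (ICC) as high as 0.05 to achieve 80% power". The result is that "the estimated required sample size for the full study is 238 patients (119 per group), which will require a minimum of 14 clusters". The article does not state alpha, so two-sided 0.05 is assumed throughout.

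Elsewhere the article describes a larger set of clusters. The abstract and Setting give 22 sites, "with 21 of the 22 sites currently enrolling participants". Randomization explains the growth: 14 sites were invited at the outset and 8 joined later. Trial Design makes each site one cluster. Outcome Data Analysis specifies multilevel models with site as the cluster level.

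**The concern.** The section ties five things together: 0.5 SD, ICC up to 0.05, 238 analysed patients, at least 14 clusters of unequal size, and 80% power. That combination can be checked, and it looked too favourable.

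In a cluster-randomised trial the arm effect is judged against variation between sites. With 14 sites that leaves about 12 degrees of freedom, and a calculation based on the normal distribution overstates power. The room left for unequal sizes also looked small for a mix of large public clinics and community private practices. Finally, the figure belongs to the original 14 sites and was not carried over to 22.

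At stake is how the result will be read. A null finding would be judged against 80% power that the stated minimum does not provide, and readers have no figure for the trial actually being run.

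**Working it through.** **Inputs from the article.** Difference 0.5 SD; ICC 0.05 (ρ); N = 238 analysed (119 per group); 14 clusters in the sample size section; 22 sites, 21 of them enrolling, in Setting; 1:1 allocation by site.

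**Assumptions.** Two-sided alpha 0.05; CV shown over a range because the article gives none; degrees of freedom = clusters − 2; equal patient numbers per arm; no gain from baseline adjustment, since the calculation claims none.

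**Formulas.** With k clusters and mean size m = 238/k:
- Design effect: DE = 1 + [(1 + CV²)m − 1] × ρ
- Standard error in SD units: SE = √(4 × DE/238)
- Noncentrality: λ = 0.5/SE
- Power: Φ(λ − 1.96) by normal approximation, or noncentral t with k − 2 df

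**Step 1: reproduce the plan's figure.** Individual randomisation needs 2(1.960 + 0.842)²/0.25 = 62.8, so 63 per arm (64 with a t-test). With 14 clusters, m = 238/14 = 17. For equal sizes DE = 1 + 16 × 0.05 = 1.80, SE = √(7.2/238) = 0.174 and λ = 2.875. Normal-approximation power is Φ(0.915) = 82.0%.

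At m = 17, equal clusters need 63 × 1.80 = 113.4 or 64 × 1.80 = 115.2 per arm. The stated 119 is therefore above the equal-cluster requirement. The implied design effect is 119/64 = 1.859 (CV about 0.26) or 119/63 = 1.889 (CV about 0.32). By normal approximation, power with 14 clusters is 80.4% at CV 0.3, reaches 80% at about CV 0.33, and falls to 77.6% at CV 0.5.

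The follow-on figures also reproduce: 238/0.8 = 297.5, so 298; 298/0.7 = 425.7, so 426.

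**Step 2: the same design on 12 df.** The critical value rises from 1.96 to 2.179.

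| CV | DE | Normal approximation | t, 12 df |
|---|---|---|---|
| 0 | 1.80 | 82.0% | 75.2% |
| 0.3 | 1.88 | 80.4% | 73.4% |
| 0.5 | 2.01 | 77.6% | 70.4% |
| 0.65 | 2.16 | 74.7% | 67.4% |

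With 14 equal clusters on 12 df, 80% is kept only up to an ICC of about 0.037. At ICC 0.05 and 238 patients, 16 equal clusters give 78.7% and 18 give 81.4%, so about 18 are needed when each arm has the same number of sites.

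**Step 3: the trial as it now stands.** With 22 sites, m = 238/22 = 10.8 and df = 20.

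| CV | DE | t, 20 df |
|---|---|---|
| 0 | 1.49 | 85.2% |
| 0.5 | 1.63 | 82.0% |
| 0.64 | 1.71 | 80.0% |
| 0.8 | 1.84 | 77.2% |
| 1.0 | 2.03 | 73.0% |

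With 21 sites (19 df), power is 84.4% at CV 0 and 81.1% at CV 0.5, and falls below 80% at a CV of about 0.58.

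**The case against.** The strongest reply is that the trial being run has 22 sites, not 14. With the t correction applied, 22 sites keep 80% up to a CV of about 0.64. No document gives site sizes, so a higher CV is conjecture. This stands, and it limits the point. A reader might infer that the running trial is underpowered; the article does not support that.

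A reader might also infer from 238 = 14 × 17 that unequal sizes were ignored. That is not shown either. The 119 per group exceeds the equal-cluster need and fits a CV of about 0.26 to 0.33, so some allowance may well have been made. Whether it is generous enough is a matter of judgement.

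Next, a condensed article commonly leaves the CV and the degrees-of-freedom method to the full protocol or SAP. That is accepted: their absence is not counted here. What counts is that the stated combination does not give the stated power.

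The 14 may be a feasibility figure, since the sentence reads "which will require a minimum of 14 clusters for sufficient recruitment". Even so, it appears as the cluster count that goes with 238 patients and 80% power, and more sites were needed for that.

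Last, the inputs may be cautious. The ICC is an upper limit, and at 0.03 14 equal clusters give 83% on 12 df. Baseline adjustment could also help: if the correlation with baseline were 0.5, with variance reduced at both levels (an assumption), 14 clusters would give 86% at CV 0 and 82% at CV 0.5. Both are fair reasons to expect better power in practice. But the article's claim is made at ICC 0.05, and its calculation takes no credit for baseline adjustment.

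**Conclusion.** The point holds for the stated 14-cluster minimum. At ICC 0.05 with 238 analysed patients, power is about 75% with equal clusters and about 70% to 73% at CV 0.3 to 0.5, against the stated 80%. This rests on two-sided alpha 0.05 and clusters − 2 degrees of freedom. The first is a conventional assumption; the second follows from randomising whole sites. Even by normal approximation, the claim fails above a CV of about 0.33.

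For the current 22 sites the section gives no figure. Power there is probably adequate, and the shortfall would carry over only if site sizes vary strongly: CV above about 0.64 with 22 sites, or about 0.58 with 21. This is a stated figure that should be corrected. It is not evidence that the trial needs more patients.

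**What to change.** - **Power statement.** In Sample Size and Power, restate power for the 21 or 22 actual sites with 238 analysed patients, ICC 0.05, the CV observed in recruitment to date, stated alpha, and a t reference with clusters − 2 degrees of freedom.
- **Cluster minimum.** Remove the 14-cluster minimum as a condition for 80% power, or correct it (about 18 equal clusters for 238 patients).
- **Primary model.** Use a matching small-sample degrees-of-freedom method, such as Kenward-Roger, so that the test agrees with the power calculation.

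The cost is a rewritten paragraph and one line on the model. Enrolment does not change. The only downside is that the published figure may turn out less favourable if the observed CV is high; in that case, prespecified adjustment for baseline AQoL-8D is a way to recover power without more patients.

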### Analysis

#### Missing Data

##### General Principles

We will exclude patients for whom only baseline data has been collected. To remain within the primary outcome analysis, patients will need to have completed the Web-based questionnaires across at least three time points (including baseline measures). For each measure, we will summarize the frequency of missing data and assess how this affects the effective sample size and statistical power. If systematic issues are identified, the study statistician and the chief investigator will discuss the findings. Otherwise, appropriate statistical imputation methods will be used to address missing data.

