### Research Objectives

The overall aim of this study is to assess the impact of systematic use of myAID by eligible patients with UC on patient-reported UC clinical outcomes over a period of up to 12 months. Specific objectives of this study are as follows:

Comparison of changes in health-related QoL (primary outcome) from baseline to 6-month follow-up in patients accessing myAID (intervention arm) versus patients receiving usual care.Comparison of differences in patient empowerment, quality of decision making, anxiety, work productivity, and disease activity including steroid use, hospital visits, and colectomy (secondary outcomes) in patients accessing myAID versus patients receiving usual care at the 6-month follow-up.Determine the predictors of health literacy in patients with UC and the relationship between health literacy, decisional conflict, and treatment choices.Determine the cost-effectiveness of implementing myAID in routine practice.Investigate the views of study participants about myAID and determine areas for improvement or barriers to implementation in clinical practice.

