#### Study Flow and Data Collection

All patients completing their baseline Web-based questionnaire will be entered into the study database and continue to be followed up by the myAID study group for 12 months unless they withdraw their consent. All participating sites will continue to provide usual care, although we will ask that a brief follow-up, either in the form of a face-to-face or telephone consultation (referred to as a *decision consult*), be arranged at 2-4 weeks after patient referral to the study if possible. Although not mandated for the study, this was felt to be important by clinicians in our pilot study to facilitate SDM.

Web-based questionnaires (using the SurveyMonkey platform) are administered to study participants at baseline, 2-4 weeks (or following the *decision consult* if arranged), 2 months, 6 months (primary and secondary outcome assessment), and 12 months (long-term impact). Table 1 summarizes the outcome measures captured at each timepoint. Study participants will be sent a URL for the questionnaires via email at each of these time points, as this was deemed acceptable and feasible from the pilot study ([name] et al, unpublished data, 2020).

All participants will be asked to submit their stool samples at baseline, 2 months, 6 months, and 12 months. Each site will provide the study participant with a preassembled stool sampling kit at the time of referral. Study participants will be asked to submit their samples to their local Sonic Healthcare pathology laboratory (nationwide pathology provider owned by Sonic Healthcare Limited), where the FC will be measured using a quantitative fluoroenzyoimmunoassay (EliA Calprotectin 2; Thermo Fisher). Participants residing outside of Adelaide in South Australia will use the SA Pathology laboratory (statewide pathology provider for the public health sector in South Australia) that uses the same assay for FC testing. Participants who do not have access to either of these labs will be asked to submit their samples to an alternative local pathology lab. All FC measurements will be performed according to the manufacturer’s instructions without knowledge of patient data. Concentrations will be expressed as micrograms per gram of stool.

We will accept patient referrals until 2020 to reach our target recruitment sample and follow-up participants for up to 12 months, thereby completing data collection in 2021.

**Table 1 table1:** myAID study outcome measures.

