Outcome measures	Baseline (within 3 weeks of referral)	Within 4 weeks	2 months	6 months	12 months
Assessment of Quality of Life-8D	✓^a^	N/A^b^	✓	✓	✓
Health Education Impact Questionnaire	✓	N/A	✓	✓	✓
Health Literacy Questionnaire	✓	N/A	✓	✓	✓
Decisional Conflict Scale	✓	✓	✓	✓	✓
Trust in Physician Scale	✓	✓	✓	✓	✓
Hospital Anxiety and Depression Scale-Anxiety	✓	✓	✓	✓	✓
Simple Clinical Colitis Activity Index	✓	N/A	✓	✓	✓
Fecal calprotectin	✓	N/A	✓	✓	✓
Clinical outcomes	✓	N/A	✓	✓	✓
Work productivity and activity index	✓	N/A	✓	✓	✓
myAID acceptability	N/A	✓	N/A	N/A	N/A

^a^✓: included.

^b^N/A: not applicable.

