##### Outcome Data Analysis

The primary analysis will be by *intention to treat* and conducted using multilevel models to account for the correlation of outcomes within a cluster (site). For the primary outcome, the dependent variable will be the AQoL-8D utility score and the exposure variable will be the intervention status (intervention vs control). The unit of analysis will be at the patient level to accommodate the weighting required by unequal cluster (site) sizes. Other independent variables will be added to the models if they are independently associated with AQoL-8D. Multilevel models will also be used to evaluate secondary outcomes.

Multilevel models will further be used to analyze each of the health literacy scores, adjusting for the participant’s age, ethnicity, educational/work status, location (rural vs urban), insurance status, and health status including anxiety and disease activity. All statistical analyses will be performed using SAS 9.4 (SAS Institute).

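### The three-time-point rule makes the primary analysis a completer set rather than the stated intention-to-treat set, and it can drop a patient whose 6-month AQoL-8D was observed

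*Protocol article*

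**What the plan says.** Four parts of the protocol article bear on this.

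- **Analysis set, as named.** Outcome Data Analysis: "The primary analysis will be by *intention to treat* and conducted using multilevel models".
- **Analysis set, as defined.** Missing Data, General Principles: "We will exclude patients for whom only baseline data has been collected". For the primary outcome, it adds that "patients will need to have completed the Web-based questionnaires across at least three time points (including baseline measures"). Baseline counts as one time point, so two post-baseline questionnaires are needed.
- **Who is enrolled and followed.** Study Flow and Data Collection: "All patients completing their baseline Web-based questionnaire will be entered into the study database and continue to be followed up". The Withdrawal section keeps participants who miss an assessment.
- **Endpoint and schedule.** Research Objectives sets the primary comparison: "Comparison of changes in health-related QoL (primary outcome) from baseline to 6-month follow-up". Questionnaires go out at baseline and 2-4 weeks, then at "2 months, 6 months (primary and secondary outcome assessment), and 12 months (long-term impact"). In Table 1, the row "Assessment of Quality of Life-8D" is ticked at baseline, 2, 6 and 12 months, and is marked not applicable for the form within 4 weeks.

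External Imputation of Outcome Measures plans regression imputation when a whole questionnaire is missing. No section exempts a patient whose 6-month score was observed, and none describes a modified intention-to-treat set or a full-set sensitivity analysis.

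**The concern.** An intention-to-treat set is fixed by allocation and enrolment. This one is fixed by what patients do afterwards, so the label and the rule cannot both stand.

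The trial is open label, and the arms are asked for different things at a time point that the rule counts. Only intervention patients view a tool of about 32 minutes, confirm that viewing through the questionnaire, and answer acceptability items at 2-4 weeks. The Introduction itself notes high attrition with electronic health technologies. Completion could plausibly differ by arm in either direction. If those who complete differ in quality of life from those who do not, selecting on completion biases the arm difference.

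The rule also counts questionnaires rather than AQoL-8D scores, and does not ask whether the 6-month score is among them. It can discard a known primary outcome while keeping a patient whose primary outcome must be imputed.

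**Working it through.** **1. The plan's own figures.** Inputs from Sample Size and Power: 0.5 SD difference, 80% power, ICC 0.05, 14 clusters, unequal cluster sizes, 20% loss at 6 months, 70% consent. Two-sided alpha of 0.05 is my assumption.

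- Individually randomised n per arm: 2 × ((1.96 + 0.84)/0.5)² = 62.8, so 63.
- Mean cluster size: 238/14 = 17. With an assumed cluster-size CV of 0.32, the design effect is 1 + ((1 + 0.32²) × 17 − 1) × 0.05 = 1.887.
- 63 × 1.887 = 118.9, so 119 per arm and 238 in total.
- 238/0.80 = 297.5, so 298 recruited. 298/0.70 = 425.7, so 426 approached.

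The stated figures reproduce. The point concerns who is analysed, not this calculation.

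**2. What the rule does, pattern by pattern.** Four post-baseline questionnaires (2-4 weeks, 2, 6 and 12 months) give 2⁴ = 16 completion patterns. With baseline counted, the rule needs at least two of the four.

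- Five patterns are excluded: none completed, or exactly one. One of the five is 6 months only, where both AQoL-8D values of the primary contrast are observed.
- Eleven are kept. Four of these have no 6-month score: 2-4 weeks + 2 months; 2-4 weeks + 12 months; 2 + 12 months; and 2-4 weeks + 2 + 12 months. In the second, no AQoL-8D exists between baseline and 12 months.
- Take two patients who by month 6 have both answered only at baseline and 6 months. The one who later answers at 12 months stays, and the other is removed. An event after the primary endpoint decides.

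**3. How many patients.** The document gives only the 20% loss at 6 months, so the following is illustrative. Let each post-baseline questionnaire be missing independently with probability q, among 298 recruited.

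- Excluded by the rule: 298 × (q⁴ + 4q³(1 − q)).
- Excluded with the 6-month score observed: 298 × q³(1 − q).
- The same if the 12-month form did not count: 298 × q²(1 − q).

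| q | Excluded | Of these, 6-month score observed | 6-month score observed but excluded, 12-month form not counted |
|---|---|---|---|
| 0.1 | 1.1 | 0.3 | 2.7 |
| 0.2 | 8.1 | 1.9 | 9.5 |
| 0.3 | 24.9 | 5.6 | 18.8 |
| 0.4 | 53.4 | 11.4 | 28.6 |

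**4. Power.** With 14 clusters and CV 0.32, power is 80.2% at 238 analysed. It is 79.1% if the analysed number is 5% lower and 78.0% if it is 10% lower.

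**5. Bias, in form only.** Let p_I and p_C be the proportions excluded in the two arms, and d the amount in SD by which retained patients score higher than excluded ones. The retained mean in an arm exceeds the full mean by p × d, so the arm difference is shifted by (p_I − p_C) × d. With purely hypothetical values of 15% and 8%, and d of 0.5 to 1.0 SD, the shift is 0.07 × 0.5 = 0.035 to 0.07 × 1.0 = 0.07 SD. That is 7% to 14% of the 0.5 SD target.

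**The case against.** The best defence is that the plan does much to limit missing data and handle what remains. Incomplete questionnaires are flagged and chased, patients who miss an assessment are kept in follow-up, and whole missing questionnaires are imputed. Missingness is summarised for each measure with its effect on sample size and power, and systematic problems go to the statistician and chief investigator. These steps should keep the number affected low, and that part stands. They do not cure the rule. Imputation serves those who remain in the analysis, and General Principles decides who remains. Nor is this a detail left to a statistical analysis plan: two explicit statements in the same article disagree.

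A reader might go further and infer that the rule takes the sample below 238. The document does not support that. Suppose dropout is monotone, at an assumed 5% before the 2-4 week form, 12% by month 2 and 20% by month 6. The rule then removes 12% of 298, about 36, leaving 262. Those 36 already lie within the 20% loss allowance. None of them has any post-baseline AQoL-8D, so no observed endpoint is wasted in that scenario.

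A reader might also take 0.035 to 0.07 SD as the bias to expect. Every rate behind it is assumed. It also counts patients with no follow-up AQoL-8D, who add little to any model, so part of such a bias could survive the fix.

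**Conclusion.** The contradiction holds as written. The primary set is defined by questionnaire completion after allocation, is labelled intention to treat, and is not aligned with the 6-month endpoint. This follows from the text alone and needs no assumption.

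The consequence is a threat to validity rather than to power. Its size cannot be known from the document, because it depends on how completion differs by arm and on how completers differ from the rest. The direct loss of observed 6-month scores is probably small: about 0.3 to 11 of 298 under independent missingness of 10% to 40% per questionnaire, both the rates and the independence being assumed. The rule should still be corrected before outcomes are seen by arm, since it fixes the primary analysis set.

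**What to change.** - Remove the three-time-point and baseline-only exclusions from the primary analysis.
- Define the primary set as every consented patient with a completed baseline questionnaire, analysed in the arm of their site.
- Use every observed AQoL-8D value in the planned multilevel analysis, with the arm contrast at 6 months.
- Handle missing scores either by the imputation already planned or by a longitudinal multilevel model under missing at random. Either can serve; the contradiction does not require one particular model.
- Keep the three-time-point set as a labelled sensitivity analysis.

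The cost is a change of wording and one additional analysis, with no new data. Patients with no post-baseline AQoL-8D will still contribute little information, and the report should give their number by arm.
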